### Analysis of primary outcome

An ordinal regression model on the total range of the mRS will be performed as the first analysis of primary outcome, under the assumption of proportional odds
[7]. The distribution of primary outcome (for example, functional outcome on the mRS) in both treatment groups will be expressed in a histogram (Figure 
4). Both adjusted and unadjusted analyses will be performed and reported. In clinical trials, adjusting for prognostic covariates improves statistical power, can correct for imbalances in baseline prognostic variables and can reduce variability in data
[17, 18]. The choice of prognostic covariates is mostly based on imbalances across treatment groups, prognostic factors that are related to the primary outcome, or a combination of both
[17]. As the investigators are blinded for all outcome data until the statistical analysis plan is accepted for publication, we chose to use the most important prognostic factors for outcome after stroke: age, stroke severity on the NIHSS, history of stroke, history of diabetes, prior disability as defined on mRS, and stroke type
[19]. Stratification of randomization was performed according to both study center and stroke severity, so we will also include study center as a covariate. The second analysis of the primary endpoint, that is, the dichotomized score on the mRS (for example, favorable versus unfavorable, mRS 0 to 2 versus mRS 3 to 6), will be expressed as OR with 95% confidence intervals (CI; Table 
4). Results of the dichotomized approach will be compared to the results of the primary analysis of primary outcome.

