### Summary study protocol

PASS is a multicenter prospective, randomized, phase III, open-label, blinded end-point superiority trial (PROBE) of standard care with preventive ceftriaxone treatment compared to standard care without preventive ceftriaxone. Adult patients with stroke (both ischemic and hemorrhagic), a score ≥1 on the National Institutes of Health Stroke Scale (NIHSS) and stroke onset within 24 hours were included
[8]. Patients were excluded in case of infection at admission, use of antibiotics within 24 hours before admission, previous hypersensitivity or anaphylaxis to cephalosporins or penicillin, subarachnoid hemorrhage, pregnancy or when death seemed imminent. Patients were randomly assigned to either ceftriaxone at a dose of 2 g, given every 24 h intravenously for 4 days, in addition to stroke-unit care, or standard stroke-unit care without preventive antibiotic therapy. Randomization was performed through ALEA (online software for randomized trials;
https://nl.tenalea.net/amc/ALEA/Login.aspx) and is based on a uniform distribution; weight of the arms is equal (1:1). Randomization is stratified according to study center (academic hospital, large non-academic hospital, or small non-academic hospital) and stroke severity (score on NIHSS 1 to 9 or >9) and performed by using random blocks with a maximum block size of 6; blocks of 2, 4 and 6 are made per stratum combination

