### Analysis of secondary outcomes

The number of patients with one or more in-hospital post-stroke infection(s) will be presented as numbers with event of numbers evaluated and analyzed using the chi-square test, and OR estimates with 95% CI. Infection rates will be reported as ‘judged by treating physicians’ and ‘infectious diseases panel.’ Death rate at discharge and at 3 months will also be analyzed using the chi-squared test and presented as OR estimates and 95% CI. Use of antibiotics in defined daily doses and length of hospital admission will be analyzed using the two group t-test or Mann- Whitney test where appropriate (Table 
4). The analysis of volume of post-stroke care, use of antibiotics during 3 months follow-up and the cost-effectiveness analysis will be analyzed using a separate analysis protocol and presented in a subsequent paper and is, therefore, not discussed here.

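### The plan runs adjusted and unadjusted ordinal models without naming which one is the primary test, and tests infection and death without using the randomization strata

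*SAP article*

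**What the plan says.** Under Analysis of primary outcome, the SAP article states: "An ordinal regression model on the total range of the mRS will be performed as the first analysis of primary outcome", assuming proportional odds. It continues: "Both adjusted and unadjusted analyses will be performed and reported". It argues that adjustment improves power and corrects chance imbalance, and lists the covariates as "age, stroke severity on the NIHSS, history of stroke, history of diabetes, prior disability as defined on mRS, and stroke type". It then adds centre: "Stratification of randomization was performed according to both study center and stroke severity, so we will also include study center as a covariate".

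The Summary study protocol section describes the strata: "Randomization is stratified according to study center (academic hospital, large non-academic hospital, or small non-academic hospital) and stroke severity", the latter split at NIHSS 1 to 9 or above 9. The same section gives one two-sided 0.05 level with 80% power and 2,550 patients.

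Under Analysis of secondary outcomes, infection is analysed by chi-square with odds ratio and 95% CI, and "Death rate at discharge and at 3 months will also be analyzed using the chi-squared test". Antibiotic use and length of stay go to a t-test or Mann-Whitney test. None of these uses the strata or the covariates.

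**The concern.** A confirmatory trial with one alpha needs one deciding test. Two P values for the same question, with no order between them, leave the choice to be made after the code is broken, in an open-label trial that the investigators themselves analyse with a biostatistician's help. The gap carries forward. The subgroup section speaks of one odds ratio per subgroup from the ordinal model, and Table 4 has one P and one odds ratio column for the dichotomized mRS; neither says which version is meant.

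Two things are at stake for the primary outcome: a modest loss of error control if either P value may count, and lost power if the unadjusted model turns out to decide. For infection and death, an analysis that ignores the stratification uses a variance that is too large for the design.

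**Working it through.** **Is a deciding model named?** The ordinal model is called the first analysis, which ranks it above the dichotomized analysis but does not separate its adjusted and unadjusted versions. The reasons for adjusting support including covariates; they do not assign the 0.05 test. No other section does so.

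**The plan's own figure.** The article gives 2,550 patients but neither the assumed effect nor the control mRS distribution, so the figure cannot be rebuilt here, and it does not show which model was powered. The calculations below therefore rest on assumed covariate strength and stratum risks.

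**Error rate if either P < 0.05 counts: normal approximation.** Let R² be the share of mRS variance explained by the covariates (assumed). The two z statistics then have correlation √(1−R²), and the error is 1 − P(both |z| ≤ 1.96):

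| R² | correlation | P(either) |
|---|---|---|
| 0.1 | 0.949 | 0.065 |
| 0.2 | 0.894 | 0.071 |
| 0.3 | 0.837 | 0.076 |
| 0.4 | 0.775 | 0.080 |
| 0.5 | 0.707 | 0.083 |

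This gives the unadjusted test an exact 5% error, which is not so after stratified randomization.

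**Error rate: simulation with stratification.** Seven-level outcome, proportional odds, no treatment effect, 1:1 allocation balanced within two severity strata, 800 patients, 6,000 replicates, one prognostic covariate with log odds ratio b per SD (assumed):

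| b | unadjusted | adjusted | either |
|---|---|---|---|
| 0.8 | 0.042 | 0.054 | 0.063 |
| 1.2 | 0.026 | 0.047 | 0.055 |
| 1.6 | 0.024 | 0.051 | 0.059 |

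The simulation standard error near 5% is √(0.05 × 0.95/6000) = 0.003, so the adjusted test is consistent with 5%. Allowing either test adds 0.8 to 0.9 percentage points to the adjusted test alone (0.0632 − 0.0540, 0.0547 − 0.0467, 0.0587 − 0.0507). The simulation's only covariate is the stratified one. The plan also adjusts for age, prior disability and others that stratification does not balance, so the real figure may lie above the simulated one and towards the approximation.

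**Power.** If the unadjusted test has 80% power, its expected z is 1.96 + 0.84 = 2.80. In a linear approximation the adjusted power is Φ(2.80/√(1−R²) − 1.96):
- R² = 0.2: 0.879
- R² = 0.3: 0.918
- R² = 0.4: 0.951

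This too ignores stratification, under which the unadjusted estimate varies less than its standard error suggests. Its real power would then be somewhat above 80% and the gap smaller.

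**Chi-squared for infection and death.** With allocation balanced within strata, the true variance is proportional to the weighted mean of p(1−p) within strata, while chi-squared uses p(1−p) at the overall risk. Assume 70% of patients at 15% risk and 30% at 45%:
- Overall risk: 0.7 × 0.15 + 0.3 × 0.45 = 0.24, so p(1−p) = 0.1824.
- Within strata: 0.7 × 0.1275 + 0.3 × 0.2475 = 0.1635.
- Ratio: 0.1635/0.1824 = 0.896.
- True alpha: 2 × (1 − Φ(1.96/√0.896)) = 0.038.
- Interval too wide by a factor of 1/√0.896 = 1.056.

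Simulated type I error (2,550 patients, 200,000 replicates) for other assumed stratum risks:

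| lower / higher risk | share at higher risk | type I error |
|---|---|---|
| 10% / 30% | 30% | 0.043 |
| 20% / 50% | 33% | 0.039 |
| 5% / 40% | 30% | 0.029 |
| 15% / 65% | 30% | 0.024 |
| 10% / 60% | 40% | 0.020 |

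**The case against.** The harm on the primary outcome is conditional. Nothing in the plan says that success on either model suffices. Outcome scale, model and covariate list are fixed before unblinding, and both results will be published, so a reader would see any disagreement. The argument for adjustment suggests which model the authors prefer. All this limits the damage, but reporting both does not say which one answers the question when they fall on opposite sides of 0.05. The protocol update that the article cites is not shown and might help; even so, naming the confirmatory test is the job of the analysis plan.

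Chi-squared for secondary outcomes is common and does not produce false positives. That stands: the cost is conservatism and lost precision. It applies to infection and death, not to all secondary outcomes. The dichotomized mRS is described in the Summary study protocol section as a logistic regression, and the promise of adjusted and unadjusted analyses may cover it, so that analysis needs confirming, not replacing.

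A reader might infer that the centre covariate differs from the stratification factor, because 29 centres were added to the trial. The documents do not support this. The Summary study protocol section defines study centre in brackets as three hospital types, and the analysis section reuses the term with the stratification as its reason. What is open is only whether the covariate has three levels or about 30.

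**Conclusion.** The point holds as a gap in specification with a modest effect. No deciding model is named for the single 0.05 test. If either model could be read as the result, type I error would be about 5.5 to 6.3% in the stratified simulation. A reader might take the 7 to 8% of the normal approximation as the headline, but that calculation ignores the conservatism of the unadjusted test after stratified randomization and is better treated as an upper figure. If the unadjusted model decides, the forgone power is worthwhile: up to 88 to 95% against 80%, for R² of 0.2 to 0.4 in a linear approximation.

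For infection and death the tests are valid but conservative, with true alpha about 2 to 4%. Covariate strength and stratum risks are assumptions throughout, since the article gives neither.

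**What to change.** - State that the single primary test at two-sided 0.05 is the treatment effect in the proportional odds model adjusted for the listed covariates and the randomization strata, and that the unadjusted model is supportive.
- State that the study centre covariate is the three-level hospital category used in randomization, and whether NIHSS enters as a score, as the stratum, or both.
- Analyse infection and death by logistic regression with the strata and the same covariates, and confirm the same adjusted model for the dichotomized mRS. Keep unadjusted odds ratios and chi-squared tests as a supplement.
- Say which version fills the single columns of Table 4 and the subgroup odds ratios.

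The cost is wording only, since the article says the code stays unbroken until the plan is accepted. The variables needed are already in the plan's own covariate list or were used at randomization. The small downside is that adjusted odds ratios are conditional and not directly comparable with unadjusted ones, which is why the unadjusted ones should stay in the tables.

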**Figure 4 Fig4:**
[figure not shown]
**Graphic display of primary outcome.**

**Table 4 Tab4:** **Secondary outcomes**

	Ceftriaxone + standard care (n = …)	Standard care (n = …)	***P***	OR 95% CI
*Secondary analysis of primary outcome*				
Favorable outcome - % n/N				
*Secondary outcomes:*				
Clinical diagnosis of infection during admission – n				
- Pneumonia				
- Urinary tract infection				
- Other				
Diagnosis of infection based on expert panel - n				
- Pneumonia				
- Urinary tract infection				
- Other				
Mortality - % n/N				
- At discharge				
- At 3 months				
Length of hospital stay - days				**NA**

NA, not applicable.

### Analysis of secondary outcomes

The number of patients with one or more in-hospital post-stroke infection(s) will be presented as numbers with event of numbers evaluated and analyzed using the chi-square test, and OR estimates with 95% CI. Infection rates will be reported as ‘judged by treating physicians’ and ‘infectious diseases panel.’ Death rate at discharge and at 3 months will also be analyzed using the chi-squared test and presented as OR estimates and 95% CI. Use of antibiotics in defined daily doses and length of hospital admission will be analyzed using the two group t-test or Mann- Whitney test where appropriate (Table 
4). The analysis of volume of post-stroke care, use of antibiotics during 3 months follow-up and the cost-effectiveness analysis will be analyzed using a separate analysis protocol and presented in a subsequent paper and is, therefore, not discussed here.

### Safety outcomes

Complications of treatment, SAE’s and SUSAR’s per patient will be tabulated according to treatment group, and analyzed using the chi-squared test (Table 
5 and table 
6).

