**Flow-chart of patients.**

### Definition of intention-to-treat and per-protocol population

Main analysis will be performed according to the intention to treat (ITT) principle. The safety analysis will be performed in a per protocol (PP) analysis. If a patient was by fault randomized more than once, the first randomization outcome was used. Patients who withdrew consent directly after randomization (that is, before treatment was initiated in those randomized for ceftriaxone in addition to standard care, or within 6 hours after randomization in those randomized for standard care) will be excluded from analysis. Patients with protocol deviations in eligibility are included in the ITT analysis and will be tabulated (Table 
1). Patients not receiving their allocated treatment due to instantaneous crossover are considered protocol violations; these patients will be included in the ITT population. PP analysis will exclude patients for whom protocol deviations in treatment and eligibility were made (see protocol deviations in eligibility and protocol deviations in treatment).

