### Protocol deviations in eligibility, consent procedure, treatment

When a patient was randomized but did not adhere to inclusion or exclusion criteria, this was considered a protocol deviation regarding eligibility. Patients with protocol deviations in eligibility were included in the ITT analysis, but excluded from PP analysis.In each center, the local investigator obtained written informed consent from the patient or representative according to the PASS study protocol. Patients who withdrew consent directly after randomization were excluded from further analysis. The flow of patients is displayed in the CONSORT flowchart (Figure 
1).

Treatment allocation was regarded as carried out according to the study protocol when a patient randomized for ceftriaxone in addition to standard care received ceftriaxone 2 gram each 24 hours for 4 days. Patients were also considered as treated PP when treatment was terminated within 4 days due to discharge, death, a palliative care policy, an allergic reaction without anaphylaxis or a previous allergic reaction in medical history (see inclusion and exclusion criteria and protocol deviation in eligibility), other side effects of treatment, or when treatment with ceftriaxone was changed into treatment with another antibiotic because of an infection because these situations and what to do were all defined and described in the initial protocol
[6]. In patients allocated to standard care, treatment was carried out according to the study protocol when patients did not receive preventive antibiotic therapy.

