#### Total use of antibiotics during hospital stay

The use of antibiotics other than preventive antibiotic therapy will be recorded in the case record form. Total antibiotic use will be recorded in units of the ‘defined daily dose’ (DDD) and the number of days of use. For definitions of the DDD, classification according to the World Health Organization (WHO) will be used for each antibiotic
[13].

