**Table 6 Tab6:** **Complications of treatment**

Adverse reaction - % n/N	Ceftriaxone + standard care (n = …)	Standard care (n = …)	***P***
- Diarrhea caused by *C. difficile*			
- Allergic reaction that caused cessation of ceftriaxone			
- Infection with ceftriaxone-resistant microorganism			
- Phlebitis at place of IV-catheter			
- Elevation of liver enzymes			
- Oliguria or elevation of serum creatinine			

Total number of adverse reactions - number %.

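### The safety tests have no small-count or continuity-correction rule, so very sparse rows have no determined verdict, and the ceftriaxone-cessation row has no meaningful control comparison

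*SAP article*

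**What the plan says.** The Safety outcomes section of the SAP article says that complications, SAEs and SUSARs, counted per patient, are to be "tabulated according to treatment group, and analyzed using the chi-squared test". It points to Table 5 (SAEs) and Table 6 (complications). Both have a count and percentage for each arm and a P column. Neither has the odds ratio and 95% CI column that Table 4 gives the secondary outcomes. The sentence names SUSARs, but neither table has a row for them.

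The plan mentions no exact test, continuity correction or expected-count threshold. It does leave room for judgement elsewhere: antibiotic use and length of stay "will be analyzed using the two group t-test or Mann- Whitney test where appropriate" (Analysis of secondary outcomes). That clause covers continuous measures only.

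One row of Table 6 is "Allergic reaction that caused cessation of ceftriaxone", with a standard-care column and a P column. On the population, the article says: "The safety analysis will be performed in a per protocol (PP) analysis". For controls, "treatment was carried out according to the study protocol when patients did not receive preventive antibiotic therapy" (Protocol deviations in eligibility, consent procedure, treatment).

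**The concern.** Some Table 6 rows, such as C. difficile diarrhea or infection with a resistant organism, could plausibly have only a handful of events. In such rows the uncorrected chi-squared test, the Yates-corrected version and an exact test can fall on different sides of 0.05. All of these are compatible with the plan's sentence or are commonly substituted for it when cells are small. The P-value is the only between-arm inference planned for harms, so no interval would show how little a sparse row establishes.

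The cessation row raises a different question: whether there is anything to compare. Stopping ceftriaxone because of an allergic reaction requires having been given ceftriaxone, and standard care does not include it.

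At stake is how the harms of preventive ceftriaxone are read against any benefit.

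**Working it through.** The document states no safety event rate, P-value or error rate, so there is no figure of the plan's own to reproduce. All event counts and rates below are assumptions.

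**Inputs.** Total N = 2,550, with "weight of the arms is equal (1:1" allocation (Summary study protocol), so n = 2,550 / 2 = 1,275 per arm. As a sensitivity case, the expected 5% loss or incompleteness (Protocol developments) gives 2,550 × 0.95 / 2 ≈ 1,211 per arm.

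**Formulas.** With equal arms, T events in total and a difference of d events between arms:

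- Uncorrected: X² = N d² / [T (N − T)]
- Yates: X² = N (d − 1)² / [T (N − T)]
- Fisher: the hypergeometric probability of splits no more likely than the one observed
- Mid-P: as Fisher, but splits exactly as likely as the observed one count half

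Example, 4 v 0 (T = 4, d = 4):

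- Uncorrected: X² = 2,550 × 16 / (4 × 2,546) = 4.006, P = 0.045.
- Yates: X² = 2,550 × 9 / (4 × 2,546) = 2.254, P = 0.133.
- Fisher: P = 0.125. Mid-P: 0.062.

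**P-values, 1,275 per arm.**

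| Split | Smallest expected count | Uncorrected | Yates | Fisher | Mid-P |
|---|---|---|---|---|---|
| 3 v 0 | 1.5 | 0.083 | 0.248 | 0.250 | 0.125 |
| 4 v 0 | 2.0 | 0.045 | 0.133 | 0.125 | 0.062 |
| 5 v 0 | 2.5 | 0.025 | 0.073 | 0.062 | 0.031 |
| 6 v 0 | 3.0 | 0.014 | 0.041 | 0.031 | 0.016 |
| 7 v 1 | 4.0 | 0.034 | 0.077 | 0.070 | 0.039 |
| 9 v 2 | 5.5 | 0.034 | 0.070 | 0.065 | 0.038 |
| 130 v 100 | 115 | 0.038 | 0.045 | 0.045 | 0.038 |

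At 4 v 0, 5 v 0, 7 v 1 and 9 v 2 the uncorrected test is below 0.05 while Yates and Fisher are not. At 130 v 100 all agree. With 1,211 per arm the results are practically the same, because when T is small against N, X² is close to d² / T.

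**Type I error given the total number of events.** At nominal 5%, the uncorrected test rejects with probability 12.5% for T = 4, 6.2% for T = 5, 7.0% for T = 8, 6.5% for T = 11 and 5.7% for T = 14. For every other total from 1 to 15 it is below 5%, and it is zero for 1 to 3 events. With Yates or Fisher it never exceeds 5% over that range.

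**Long-run type I error (two independent binomials, same true rate, 1,275 per arm).**

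| True rate | Expected events per arm | Uncorrected | Yates | Fisher |
|---|---|---|---|---|
| 0.05% | 0.64 | 0.4% | 0.01% | 0.01% |
| 0.1% | 1.28 | 2.3% | 0.1% | 0.1% |
| 0.2% | 2.55 | 4.6% | 0.9% | 0.9% |
| 0.5% | 6.38 | 4.4% | 2.3% | 2.5% |
| 1% | 12.75 | 5.2% | 2.8% | 3.0% |
| 2% | 25.50 | 5.0% | 3.5% | 3.5% |

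**The cessation row.** A per-protocol control has had no preventive antibiotic. Treatment antibiotics are allowed and captured: "The use of antibiotics other than preventive antibiotic therapy will be recorded in the case record form" (Total use of antibiotics during hospital stay), though the drugs are not named. A control could therefore have this event only if ceftriaxone was given to treat an infection and then stopped for allergy. In the ceftriaxone arm, patients who stopped early for an allergic reaction without anaphylaxis stay in the per-protocol set, so their events count. The row compares a group exposed by design with one almost entirely unexposed. With 6 v 0, every test in the first table gives P < 0.05, and that result would reflect little beyond who was given the drug.

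**The case against.** The strongest reply is that a chi-squared test is a defensible choice here. A reader might infer from 4 v 0 that the plan produces P-values that are too small and inflates false alarms of harm. The documents do not support that reading. The total number of events is not known in advance, so the error rate that matters for a plan is the long-run one, and with equal arms it stays at about 5% or less. The conditional excess occurs at a few totals only. If the analysts apply Yates correction, which the plan neither states nor excludes, every reversal above disappears. The event counts are also assumed. All of this stands.

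A blanket switch to Fisher's test would have a real cost: its size is 0.1% at a 0.1% event rate and 0.9% at 0.2%, so a true harm becomes harder to detect. That also stands and shapes the remedy.

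A reader might also say that controls cannot have the cessation event at all. That is too strong, since therapeutic ceftriaxone is not excluded. It is a near-structural zero, and the P-value remains uninformative because controls as a group are not at risk.

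Finally, a journal article may leave small-cell detail to a fuller plan, and readers can recompute tests from the n/N in the tables. Neither reply settles the matter. The article states the test outright while leaving the correction open, and recomputation by readers is not prespecification.

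**Conclusion.** The point holds in a limited form. For very sparse rows the plan does not determine whether a result is reported as significant: 4 v 0 is P = 0.045, 0.133 or 0.125 depending on an unstated choice, and no interval is planned alongside it. This rests on assumed counts and about 1,275 per arm, and it does not touch rows with many events. It is a gap in prespecification, not an inflation of type I error. The between-arm P-value for the ceftriaxone-cessation row is uninformative whichever test is used, and this part does not depend on the assumed counts. The matter is minor to moderate. It concerns the safety tables only and leaves the primary result unaffected.

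**What to change.** Amend the Safety outcomes section and the layout of Tables 5 and 6:

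- Report each row with a risk difference and a 95% CI by a method suited to small counts.
- Where any expected cell count is below 5, use an exact test, preferably a mid-P or unconditional exact version to limit conservatism.
- For the remaining rows, state whether the chi-squared test is continuity-corrected. This matters just above the threshold: 9 v 2 has an expected count of 5.5 and still gives 0.034 or 0.070.
- For the ceftriaxone-cessation row, give the incidence in the ceftriaxone arm with an exact CI and no P-value.

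The cost is a few sentences, one more table column and a little more analysis work. If Fisher's test is chosen instead of mid-P or an unconditional version, some sensitivity is lost in the rarest rows. General analysis principles keeps the code unbroken until the plan is accepted, so the wording can be settled blind.
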